## Background

Musculoskeletal pain in pregnant women is often regarded as something that is transient, physiological, and self-limiting, but low back pain (LBP) and pelvic girdle pain (PGP) during pregnancy are associated with an increased risk of suffering these pains in future pregnancies and of the pain becoming chronic [1].

Low back pain is usually defined as occurring between the twelfth rib and the gluteal fold. Pelvic girdle pain is experienced between the posterior iliac crest and the gluteal fold, particularly in the vicinity of the sacroiliac joints. The pain may radiate to the back of the thigh and may occur in isolation or be associated with pain in the symphysis pubis [2]. Opinions are divided as to whether LBP and PGP should be associated or differentiated. According to some experts, they can be differentiated clinically, responding to different treatments and having different risk factors [3]. However, studies have so far failed to distinguish reliably between the two, and LBP is very likely to be a subgroup of the pelvic pain associated with pregnancy [4]. In fact, similar pathophysiological mechanisms – joint laxity, increased lumbar lordosis, and muscle weakness – have been suggested to be at the cause of both conditions [5-7].

About 45% of all pregnant women suffer from LBP and/or PGP (LBPGP) [8]. The prevalence appears to be somewhat higher in the Nordic countries [9], and higher still in Spain, where the prevalence at 4 weeks is estimated to be 71.3% for LBP and 64.7% for PGP [10]. LBPGP usually begins from week 18 of pregnancy, and although it may appear in the first quarter, the peak intensity is from weeks 24 to 36 [8].

There are three major risk factors for the development of LBPGP during pregnancy: strenuous work, the presence of LBP before pregnancy, and the development of LBPGP during previous pregnancies [8]. On the other hand, the use of contraceptives, the period of time elapsed since the last pregnancy, maternal height and weight, smoking, and age [2] are not usually considered risk factors, and neither the use of epidural or spinal anaesthesia or analgesia seem to be relevant [11].

LBPGP hampers women’s everyday activities, such as getting up, turning over in bed, sitting down, walking, dressing and undressing, lifting, and carrying small objects. It can also impede sexual relations, render subjects unable to work [12,13], and, in general, negatively affect their quality of life [14].

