### Statistical analysis

A descriptive analysis will be performed to assess the comparability of the four groups with regard to baseline demographic information, prognostic variables, and the evaluation of credibility, using measures of central tendency and dispersion for the quantitative variables and frequency distributions for the qualitative ones.

To determine the primary study outcome (change in pain intensity at 2 weeks) and secondary outcomes (change at 2 weeks in functional status with respect to pain, quality of life, and improvement perceived by the patient), a crude analysis will be performed to compare the mean differences between baseline values and at 2 weeks, for the VAAc group and the SOC group, using the Student *t*-test for independent samples or the Mann-Whitney U test if the samples do not present a normal distribution (determined by the Shapiro-Wilk test). Subsequently, simple and multivariate linear regression analyses will be performed, using the same outcome variables, to adjust for unbalanced independent variables, including the treatment group in the first pass, and determining regression coefficients with the corresponding 95% confidence intervals and the coefficient of determination. The main analysis will be by intention-to-treat, but a per protocol analysis will also be performed.

To determine the secondary outcomes of presence of temporary occupational incapacity, reduction in the consumption of analgesic medication at 2 weeks, and presence of pain at 12 and 48 weeks postpartum, the VAAc and SOC groups will be compared, using the χ^2^ test with continuity correction or Fisher’s exact test when the expected values are below 5. Then, simple and multivariate logistic regression models will be obtained, with the same outcome variables, to adjust for unbalanced independent variables, including the treatment group in the first pass, and the relative risk will be determined, with 95% confidence intervals.

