Both the quantitative outcome variables (mean differences) and the qualitative ones (difference in proportions) will be expressed with the respective 95% confidence intervals and intention-to-treat analysis criteria will be used (last known value for losses-to-study for the quantitative outcome variables, and penalisation of results in the experimental treatment for the qualitative variables). To assess the specificity of the effect of auricular acupuncture, previous analyses comparing the VAAc treatment group versus PAAc and NSAAc will be repeated. In each test, the bilateral statistical significance limit of *P* <0.01 will established. An intermediate analysis will be performed when complete tracking is concluded for half of the sample population, setting the level of bilateral statistical significance at *P* <0.005, this being a necessary penalisation to minimise type I errors.

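### The plan names logistic regression but promises relative risks for the binary secondary outcomes, with no step that links the two

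*Protocol article*

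**What the plan says.** The Statistical analysis section of the protocol article treats four secondary outcomes as binary: "presence of temporary occupational incapacity, reduction in the consumption of analgesic medication at 2 weeks, and presence of pain at 12 and 48 weeks postpartum". Verum and standard-care arms are first compared by a χ² "test with continuity correction or Fisher’s exact test when the expected values are below 5". After that, "simple and multivariate logistic regression models will be obtained, with the same outcome variables", to adjust for variables that turn out unbalanced. The same sentence ends with the measure to be reported: "and the relative risk will be determined, with 95% confidence intervals".

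The next paragraph adds a second measure for binary outcomes: "the qualitative ones (difference in proportions) will be expressed with the respective 95% confidence intervals". It also says that the analyses will be repeated for verum acupuncture against the placebo arm and against the non-specific arm.

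The article does not mention odds ratios, a log-binomial or Poisson model, standardisation, or any other route from a logistic fit to a relative risk. It neither states nor assumes an event rate for any of the four outcomes.

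**The concern.** The model and the effect measure do not belong together as written. Exponentiating a logistic coefficient gives an odds ratio. The odds ratio lies on the same side of 1 as the relative risk but further from it, and the gap widens as the outcome becomes more frequent.

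The matching sentence on the continuous outcomes reports the linear model's own coefficients with their confidence intervals. Read in the same way, the relative risk would be the logistic model's own output under the wrong name. This is an inference, but a natural one.

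What is at stake is the reported size of effect for four outcomes in up to three comparisons (4 × 3 = 12 adjusted ratios). A clinician who reads a relative risk of 0.56 takes it as a 44% reduction in risk, and that would be wrong if 0.56 were an odds ratio. For reduced analgesic use the event is favourable, so the hoped-for ratio lies above 1 and the exaggeration would run upwards.

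**Working it through.** **The plan's own figure.** The only calculated figure is the sample size for pain intensity (Sample size section: difference 20 mm, SD 25 mm, alpha 0.01 two-sided, beta 0.10).

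- n per group = 2 × [25 × (2.576 + 1.282) / 20]² = 46.5, rounded up to 47.
- With 10% loss: 47 / 0.90 = 52.2, rounded up to 53. Four arms: 4 × 53 = 212.

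Both figures reproduce. Nothing below depends on them.

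**Inputs for this point.** The model and the measure come from the Statistical analysis section. The control risks p0 are assumptions, because the article gives none for these outcomes. The true relative risk of 0.70 is also an assumption.

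**Formulas.** p1 = RR × p0, and OR = [p1/(1 − p1)] / [p0/(1 − p0)].

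Example at p0 = 0.45: p1 = 0.70 × 0.45 = 0.315. The odds are 0.315/0.685 = 0.460 and 0.45/0.55 = 0.818, so OR = 0.460/0.818 = 0.56.

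| Assumed control risk | True RR | OR | True reduction | Reduction if the OR is read as an RR |
|---|---|---|---|---|
| 5% | 0.70 | 0.69 | 30% | 31% |
| 10% | 0.70 | 0.68 | 30% | 32% |
| 20% | 0.70 | 0.65 | 30% | 35% |
| 30% | 0.70 | 0.62 | 30% | 38% |
| 45% | 0.70 | 0.56 | 30% | 44% |
| 60% | 0.70 | 0.48 | 30% | 52% |

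Up to about 10% the mislabelling would hardly matter. From 30% upwards it would.

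**A scale from the article's own background.** The Background cites an acupuncture study in which 60% against 14% of women had less intense pain. There RR = 0.60/0.14 = 4.29, while OR = (0.60/0.40)/(0.14/0.86) = 9.21. This is not one of the four outcomes. It only shows how far the two measures can separate.

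**Can a logistic fit give a valid relative risk?** Yes. In a simulated data set of 400,000 subjects with one covariate, the risks were 32.6% and 50.1%, an observed RR of 0.326/0.501 = 0.65. The adjusted odds ratio from the logistic model was 0.45. Predicting each subject's risk under both arms from that same fit, and taking the ratio of the averages, gave 0.65. The logistic model itself is therefore not the problem. What is missing is the statement of how its output becomes a relative risk.

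**The case against.** The strongest reply is that the article says only that the relative risk will be determined. It does not say that the exponentiated coefficient will be called one. Marginal standardisation gives a valid relative risk from a logistic fit, and a condensed article may leave that step to a fuller document that is not shown. This stands as far as the consequence goes: overstatement is conditional, not certain. It does not remove the mismatch, because the article itself fixes both the model and the measure in one sentence, and the model does not directly estimate the measure.

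Two stronger readings are tempting.

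- A reader might infer that these outcomes are common and that every binary secondary effect will be misreported. The article does not support this. Its prevalences of about 45%, 71.3% and 64.7% are for pain in pregnancy, not for postpartum pain, inability to work or reduced analgesic use. The difference in proportions is also planned, and as a crude measure it does not pass through the logistic model.
- A reader might also count the continuity-corrected χ² test as a fault. At 53 per arm and alpha 0.01 it is conservative: its actual size is 0.0043, 0.0050 and 0.0048 at event rates of 0.2, 0.3 and 0.5. It does control the type I error, however, whereas the uncorrected test slightly exceeds 0.01 at 0.2 and 0.3 (0.0104 and 0.0103). Statisticians reasonably differ on this choice, and it is not an error in the plan.

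**Conclusion.** The point holds as a mismatch between the named model and the named effect measure for the adjusted analysis of the four binary secondary outcomes. Effects would be overstated only if the exponentiated logistic coefficient were labelled a relative risk, and only where the outcome is not rare.

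Under an assumed true relative risk of 0.70, the figure reported would lie between 0.68 (10% control risk) and 0.48 (60% control risk). Where the trial's outcomes fall in that range is not documented. High rates are plausible for some of them, since every participant has pain at entry, but this remains an assumption.

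The primary outcome, the sample size, the crude tests and the crude differences in proportions stand as planned. The mismatch is worth correcting before the data are analysed, but it does not threaten the trial's main conclusion.

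**What to change.** State in one sentence how the adjusted relative risk and its 95% confidence interval will be obtained. Any of these would do:

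- modified Poisson regression with robust standard errors;
- a log-binomial model;
- the planned logistic model, followed by marginal standardisation to give an adjusted risk ratio and an adjusted risk difference.

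The third keeps the logistic model and gives an adjusted counterpart to the difference in proportions that is already planned. If none is wanted, replace relative risk by odds ratio in the text and in all tables. In that case, warn the reader that crude and adjusted odds ratios can differ even without confounding.

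The cost is a change of wording and the use of standard software. No further data are needed, and the sample size does not change. The one visible downside is that the reported ratios will look less extreme than odds ratios would. The choice should be fixed before the treatment allocation is revealed to the analysts.

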### Study period

February 2014 to December 2016.

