### Randomisation and blinding procedures

The four study arms will be randomised centrally, at the Costa del Sol Hospital, Research Support Unit, to achieve a 1:1:1:1 allocation ratio, stratified by healthcare centre. The health professionals taking part in the study will not be involved in the randomisation process. Patients who meet the inclusion criteria and give their signed informed consent will be included in the study. After inclusion, the researcher will contact the randomisation centre, where the patient’s data will be recorded, and the midwife will be informed, by telephone and by fax, of the patient’s allocation to one of the four study arms. This procedure ensures that randomisation will not be influenced by any of the researchers involved. The patients assigned to the VAAc, NSAAc, and PAAc groups will be blinded with respect to the treatment allocated to them.

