### Sample size

Taking Wang et al. [31] as a reference, for the primary purpose of the study, namely to compare the change in pain intensity, assessed on an iVAS, between the baseline assessment and the value at 2 weeks after the intervention, a difference of over 20 mm between the VAAc group and the SOC group will be considered statistically significant. For a known standard deviation of 25 mm for each group, a type I (alpha) error of 0.01 and a type II (beta) error of 0.10, 47 patients per group will be required. Including the patients for the PAAc and NSAAc arms, and with an estimated 10% loss to intervention follow-up, a total of 212 patients (53 per group) will need to be assessed.

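### Only the interim test is penalised: 0.005 at the look and 0.01 at the end give an overall two-sided type I error of about 0.0135, not the planned 0.01

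*Protocol article*

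**What the plan says.** All of this is in the protocol article.

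- **Final level.** The Statistical analysis section sets a two-sided limit of P<0.01 for each test. No other level is given for the final analysis.
- **Interim look.** The same section adds that "An intermediate analysis will be performed when complete tracking is concluded for half of the sample population". It sets two-sided P<0.005 for that look and explains the lower level as "this being a necessary penalisation to minimise type I errors". It does not say what may be decided at the look.
- **Sample size.** The Sample size section plans to detect "a difference of over 20 mm between the VAAc group and the SOC group", and takes the SD as 25 mm in both arms. The error rates and the resulting requirement are stated as "a type I (alpha) error of 0.01 and a type II (beta) error of 0.10, 47 patients per group will be required". Allowing for 10% losses raises this to 53 in each arm, 212 in all.
- **Timing.** The primary outcome is read 2 weeks after treatment starts (T2). Follow-up continues to 12 weeks (T3) and 48 weeks (T4) postpartum. Women enter at 24 to 36 weeks' gestation. The Study period section gives "February 2014 to December 2016", with no separate recruitment window.

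**The concern.** Lowering the level at an interim look does not by itself protect the overall error. A false positive can arise at either look. If the final test keeps the full 0.01, whatever is spent at the interim comes on top of it, less the overlap between the two tests. The article presents the 0.005 as the step that deals with type I error, yet the 0.01 was already fully used in the sample size. A claim of success would then not carry the 1% error rate that the plan states.

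The trigger is also unclear. The primary outcome is known after 2 weeks, but the look waits for *complete tracking*, which is not defined and could mean anything from T2 to T4.

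**Working it through.** **1. The plan's own sample size.** Inputs from the Sample size section: difference 20 mm, SD 25 mm, alpha 0.01, power 0.90. Two-sided normal formula:

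n = 2 × [25 × (2.576 + 1.282) / 20]² = 46.5, rounded up to 47 per group.

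47 / 0.9 = 52.2, rounded up to 53; 4 × 53 = 212. The stated figures reproduce with two-sided alpha 0.01 and no allowance for an interim look.

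**2. Overall type I error as written.** Let Z1 and Z2 be the interim and final statistics for VAAc versus SOC. Under the null hypothesis they are bivariate normal with correlation √t, where t is the information fraction. The limits are c1 = 2.807 (P<0.005) and c2 = 2.576 (P<0.01).

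Overall error = 1 − P(|Z1| ≤ 2.807 and |Z2| ≤ 2.576)

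| t | Overall two-sided error |
|---|---|
| 0.3 | 0.0142 |
| 0.5 | 0.0135 |
| 0.7 | 0.0125 |

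At t = 0.5 the look spends 0.0050 and the final test adds 0.0135 − 0.0050 = 0.0085. The excess over plan is 0.0035, or 35% of 0.01.

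**3. Pairs of levels that hold 0.01, and their power.** The final level is solved so that the overall error is 0.01 at t = 0.5. Power is for 20 mm, SD 25 mm and 47 per group: the final statistic has mean 20 / (25 × √(2/47)) = 3.878 and the interim statistic has mean 3.878 × √0.5 = 2.742.

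| Interim | Final | Overall error | Power |
|---|---|---|---|
| 0.005 | 0.01 (as written) | 0.0135 | 0.907 |
| 0.001 | 0.0094 | 0.01 | 0.901 |
| 0.005 | 0.0061 | 0.01 | 0.879 |
| 0.005 | 0.005 | 0.0090 | 0.866 |

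**4. When the look would fall.** Assumptions that the article does not state: delivery at 40 weeks and uniform accrual from February 2014. The study period is 35 months, about 152 weeks.

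- Entry to T4 takes 4 to 16 weeks to delivery plus 48, so 52 to 64 weeks.
- If every T4 falls inside the period, recruitment lasts at most 152 − 64 = 88 to 152 − 52 = 100 weeks. Half are enrolled at week 44 to 50.
- With a 52-week interval, the look is at week 50 + 52 = 102, which is 2 weeks after recruitment closes at week 100. With 64 weeks, it is at 44 + 64 = 108, which is 20 weeks after closure at week 88.

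| Reading of the trigger and period | Share recruited at the look |
|---|---|
| T4, all follow-up inside the period | 100% |
| T4, 35 months are recruitment only (look at week 128 to 140 of 152) | 84–92% |
| T3 | 66–82% |
| T2 | 52% |

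**The case against.** **No stopping or success rule is stated.** If crossing 0.005 at the interim could never support a claim, the look would spend nothing. What an interim may decide is often left to a fuller document. This stands as a condition on the 0.0135. But the article fixes both levels itself and justifies the lower one as protection against type I error, which makes sense only if crossing it counts.

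**0.005 is half of 0.01, so an even split over both looks may have been meant.** That would give 0.0090, within plan. The text does not say so: 0.005 is attached to the interim alone, and 0.01 is the only level given for the final analysis. Even on this reading, the power with 47 per group is about 0.87, below the planned 0.90.

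**The excess is small.** It is 0.0035 on an already strict level. This is true, and it limits the weight of the point. It does not make the stated control correct.

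**Two stronger readings are tempting.** A reader might infer that the look certainly comes too late to affect recruitment. That requires *complete tracking* to mean T4, all follow-up to fall inside the study period, and uniform accrual; the article states none of these. Even then the margin can vanish. With a 52-week interval, the look coincides with the last woman's T2. With 50 weeks, recruitment could run 102 weeks and the look would fall at 51 + 50 = 101, before closure. If the look did come when all T2 data existed and used them all, its information would be near 1 and the inflation would largely disappear, so the late-look reading and the 0.0135 should not be added together.

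A reader might also extend the error across the three VAAc comparisons. The sample size rests on VAAc versus SOC, the other two comparisons assess specificity, and no familywise 0.01 is promised. That is a separate matter.

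**Conclusion.** The point holds for the significance levels. As written, the overall two-sided type I error for VAAc versus SOC is 0.0135 instead of 0.01, provided that P<0.005 at the interim counts as a positive result and the look uses half of the primary-outcome information. Fractions from 0.3 to 0.7 give 0.0142 to 0.0125, so the excess does not hinge on the exact fraction. It is modest in size, but the stated penalisation does not do what the article says it does.

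The trigger is a secondary and conditional point. What the article establishes is that the term is undefined. Read as T4 with all follow-up inside the study period, the look would probably come after recruitment has closed; on a T2 or T3 reading, or if the 35 months are recruitment only, it would not.

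**What to change.** Settle the following before any interim data are seen.

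1. **Levels.** State one of these:
   - interim P<0.001 and final P<0.0094, which holds 0.01 overall and keeps power at 0.90 with 47 per group, so no women are added;
   - interim P<0.005 and final P<0.0061, with power restated as about 0.88. Restoring 0.90 takes 50 evaluable women per group (power 0.9015); 50 / 0.9 rounds up to 56 per group, or 224 in total, 12 more than planned;
   - the interim cannot support an efficacy claim, or is dropped, and the final level stays at 0.01. This leaves the sample size unchanged.
2. **Trigger.** Replace the undefined term with the 2-week primary outcome (T2) of the first 106 women (212 / 2), and say what the look may decide.

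Both changes are a sentence or two of text. Only restoring 90% power under the second option costs patients.

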### Ethical issues

The ethical validity of this study has been examined by the Regional Clinical Trials Committee. It was subsequently approved by the Research Ethics Committee (Comité de Ética de la Investigación Área Sanitaria Sevilla Sur, 20130429). The project has received funding from a public national call for proposals, awarded on a competitive basis. The study complies with the Declaration of Helsinki and subsequent updates (to the 2008 revision) and takes into account the principles set out in the Council of Europe Convention on Human Rights and Biomedicine, as well as the requirements established by Spanish legislation regarding biomedical research, the protection of personal data, and bioethics. During the course of the study, audits will be performed as required by the above-mentioned Research Ethics Committee and by the hospital’s Quality Commission, independently of any external audits (source of research funding) that may be deemed necessary. The forms, case report data, and computer data files will be identified with codes, not the names of the patients, in order to protect personal data. Statistical analysis will be performed by third parties who will be unaware of the source data (blinded analysis).

